### Recruitment {15}

This study will be conducted at West China Second Hospital, a teaching hospital in Chengdu, China. After the admission of infants who may meet the eligibility criteria, the principal investigator or a delegated deputy will explain the written informed consent to at least one parent. A senior investigator will be available at all times to address any concerns raised by parents or clinicians during the course of the trial.

## Assignment of interventions: allocation

### Allocation—sequence generation {16a} {16b}

After meticulous screening to ensure compliance with the inclusion criteria, eligible infants will be systematically randomized into one of two distinct groups: the LMA group or the INSURE group, adhering to a 1:1 allocation ratio. The randomization sequence will be computer-generated using R software (version 4.1.0, R Foundation for Statistical Computing, Vienna, Austria). To maintain allocation concealment, the randomization will be performed using sealed envelopes. Blocking will be used to enhance the balance and integrity of group assignments. In scenarios involving multiple births, each infant will undergo individual randomization to preserve the independence and validity of the study outcomes. This comprehensive approach underscores our commitment to methodological precision and the reliability of our clinical trial.

### Implementation {16c}

Upon obtaining consent, trained research coordinators will sequentially open the numbered randomization envelopes to reveal group assignments. A protocol-certified respiratory therapist will then administer the designated treatment intervention following standardized procedures. During the enrollment process, the therapist will not be blinded to the group allocation.

## Assignment of interventions: blinding

### Who will be blinded {17a}

Healthcare staff: Blinding is not feasible.

Patients and their families: Blinded.

Nurses: Blinding is not feasible.

Outcome assessors: Blinded.

Biostatisticians: Blinded.

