### Strategies to improve adherence to interventions {11c}

Before the study begins, the research team will undergo protocol-based training to ensure a clear understanding of their respective roles and responsibilities. Pediatricians will assess whether the infant meets the criteria for PS administration, respiratory therapists will be responsible for the intervention and data recording, and nurses will assist with the intervention. Data recorders will also receive training to ensure consistency in data collection. Any challenges encountered during the trial will be promptly addressed.

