### Outcomes {12}

#### Primary outcome measures

The SF index (SpO_2_/FiO_2_) at 1 day after PS administration.

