### Procedure for unblinding if needed {17b}

Blinding was implemented for both outcome assessors and biostatisticians in this trial. Outcome assessors remained blinded throughout the processes of data collection and outcome evaluation to ensure unbiased assessment. Biostatisticians were also blinded during data analysis to minimize analytical bias. In contrast, all clinical personnel and participants were aware of the treatment allocations to preserve the authenticity and integrity of the pragmatic intervention conditions.

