## Data collection and management

### Data collection methods {18a} {18b} {19}

In this trial, we have implemented a structured approach to ensure the accuracy and reliability of data collection. A standardized bedside recording form will be utilized throughout the study period. During PS administration, 2–3 designated healthcare staff members will be responsible for conducting the procedure to maintain consistency, while an additional healthcare staff member will oversee the process and meticulously record the data. This dual-layered approach not only enhances the precision of data collection but also minimizes potential errors.

After the use of PS, the monitoring of primary and secondary outcomes will continue, with bedside nurses recording data at several predetermined time points: 1 minutes, 3 hours, 6 hours, 12 hours, and 1 day after PS administration. This ongoing monitoring ensures that any post-trial developments are captured systematically. Furthermore, to ensure the integrity and comprehensiveness of the dataset, the trial leader will retrospectively review and complete any additional data entries. This meticulous methodology underscores our commitment to rigorous data management and the reliability of the trial outcomes. By employing a combination of real-time monitoring and retrospective data completion, we aim to provide a robust and comprehensive dataset that accurately reflects the trial’s findings. This approach not only enhances the validity of our results but also ensures that all relevant data points are captured and analyzed thoroughly.

The trial data will undergo rigorous verification and management under the supervision of the principal investigator (PI). To ensure data integrity and security, all collected data will be stored in a designated area within the department, specifically allocated for this trial. Upon the completion of data collection, the PI will be responsible for summarizing and organizing the data into a structured format, facilitating subsequent analysis and reporting. In addition to data management, the PI will play a pivotal role in maintaining the study’s adherence to protocols. This includes conducting regular training sessions for all trial participants, focusing on procedural accuracy and standardized data collection methods. These training initiatives aim to minimize errors, enhance consistency, and ensure that all participants are well-equipped to follow the study’s guidelines meticulously.

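### The protocol claims blinded outcome assessors during data collection, but bedside nurses it declares unblinded record the primary day-1 SF index

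*Protocol article*

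**What the plan says.** All places are in the protocol article.

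- **Primary outcome measures:** "The SF index (SpO_2_/FiO_2_) at 1 day after PS administration".
- **Who will be blinded {17a}:** "Outcome assessors: Blinded", but also "Nurses: Blinding is not feasible". Other healthcare staff are listed as unblinded too. Patients and families are listed as blinded, as are the biostatisticians.
- **Procedure for unblinding {17b}:** "Outcome assessors remained blinded throughout the processes of data collection and outcome evaluation to ensure unbiased assessment". The same paragraph says that "all clinical personnel and participants were aware of the treatment allocations".
- **Data collection methods {18a} {18b} {19}:** after surfactant, follow-up of primary and secondary outcomes continues "with bedside nurses recording data at several predetermined time points", and 1 day is one of the listed points. Later, "the trial leader will retrospectively review and complete any additional data entries". During the procedure itself, a further member of the healthcare staff does the recording.
- **Strategies to improve adherence {11c}:** "respiratory therapists will be responsible for the intervention and data recording". Under Implementation {16c} the therapist is not blinded.

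**The concern.** The protocol claims a specific protection, blinding of assessors while data are being collected, and then gives that collection to people it says cannot be blinded. For the primary outcome no other collector is named. A results paper that repeats the claim would credit the SF comparison with a safeguard it did not have.

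This matters more than usual in an equivalence trial. Unblinded recording that makes the arms look alike favours the conclusion the trial hopes to reach. Unblinded recording that favours one arm can hide equivalence that is really there. SpO2 is read from an instrument, but FiO2 is a setting and a person takes the reading. Near room air, where the planned mean SF of 4.5 lies, the ratio is sensitive to small changes in FiO2.

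Two related points come from the same sections. The statements on families and on participants disagree. The trial leader may also complete entries in retrospect, with no blinding status and no source-record condition stated for that step.

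**Working it through.** **1. The statements side by side**

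| Question | One place | Another place |
|---|---|---|
| Is collection of the day-1 SF blinded? | {17a} and {17b}: assessors blinded, data collection included | {18a}: bedside nurses record it; {17a}: nurses cannot be blinded; {17b}: all clinical staff know the arm |
| Do families know the arm? | {17a}: blinded | {17b}: participants aware |
| Who completes entries later? | {18a}: the trial leader | No blinding status or source requirement given |

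The first row cannot be reconciled by supposing a separate assessor. {17a} does not define the assessor, so a masked reader of completed forms may exist. But {17b} claims blinding during collection, and by then SpO2 and FiO2 are already written down.

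In the second row, {17b} names clinical personnel separately, and the patients are newborns. Participants there most naturally means the families.

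**2. How sensitive SF is (illustration; the plan has no figure on this point)**

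Inputs: margin 0.45 and planned mean 4.5 (Sample size {14}). Assumed, not in the protocol: SpO2 between 90% and 95%, and a systematic FiO2 difference of 0.21 versus 0.23. SF = SpO2 / FiO2.

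- SpO2 95%: 0.95/0.21 = 4.52 and 0.95/0.23 = 4.13. Difference 0.39; 0.39/0.45 = 87% of the margin.
- SpO2 90%: 0.90/0.21 = 4.29 and 0.90/0.23 = 3.91. Difference 0.37; 0.37/0.45 = 83% of the margin.

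These are changes within one infant, whereas the margin applies to a difference in group means. If a fraction p of one arm is affected, the mean shifts by p × 0.39 (SpO2 95%). With p = 1 that is 0.39. With one infant in 30 it is 0.39/30 = 0.013.

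**3. What an assumed shift in the mean would do to the equivalence test**

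Inputs: SD 0.41 and 23 per group ({14}); equivalence declared if the 90% CI lies within ±0.45 ({20a}). Standard error = 0.41 × √(2/23) = 0.121. Probabilities come from simulating the t-based two one-sided tests with 400,000 draws. The sizes of the shift are assumptions.

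| True difference | Shift from unblinded recording or setting | Chance of declaring equivalence |
|---|---|---|
| 0.45 | none | 5% |
| 0.45 | shrinks by 0.1 | 20% |
| 0.45 | shrinks by 0.2 | 49% |
| 0.45 | shrinks by 0.3 | 79% |
| 0 | none | 96% |
| 0 | spurious 0.2 | 65% |

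At SpO2 95%, a mean shift of 0.2 would need about half of one arm (0.2/0.39 = 0.51) to be affected by the two-point FiO2 difference. The last row shows that bias can also count against equivalence.

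**The case against.** The defence accepts the wording conflict and argues that little follows from it. Much of that argument stands.

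- **Who sets FiO2.** A reader might infer that the nurses who chart FiO2 also set it. The protocol does not say who sets it after surfactant. That whoever sets it is unblinded is an inference, though a firm one, because {17b} says all clinical personnel knew the arm.
- **The trial leader.** A reader might infer that SF values are filled in afterwards. {18a} speaks only of additional entries and does not name SF, and {20c} already provides multiple imputation for a missing primary outcome. The gap is the absence of a source condition, not evidence of retrospective SF values.
- **One charted value.** A reader might infer that SF rests on a single reading. The article does not say how the day-1 value is obtained, and the full protocol may.
- **Therapists as recorders.** {11c} gives them data recording, but nothing ties this to the day-1 SF. Only the sentence on nurses bears on the primary outcome.
- **Size.** The 87% is not an estimate of bias. It needs a whole arm shifted and an SpO2 that the protocol does not give.
- **Partial protection remains.** SpO2 is an instrument reading, which limits pure charting bias, and the biostatisticians are blinded.
- **Families.** Nothing suggests that their awareness would affect SF.

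None of this removes the contradiction. Nor is it a detail that an article leaves to the full protocol, since the article makes both statements outright.

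**Conclusion.** The point holds as a false statement about design. The protocol says the outcome was collected blind, and its own data collection section shows that the primary outcome is not. The conflict over families is also real but minor. The retrospective-entry provision is too loose for a primary outcome, though the protocol does not say that it covers SF.

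No size of bias can be derived from the protocol. The shift of 0.37 to 0.39 rests on assumed SpO2 values and on a systematic FiO2 difference across a whole arm. It shows only that SF near room air is sensitive enough for the recorder's blinding status to matter. A reader might conclude that unblinded staff will produce equivalence; the protocol does not support that, since the direction is unknown. The correction should be made because it changes what the trial may claim about protection from bias. It does not show the trial to be biased.

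**What to change.** 1. Correct {17a} and {17b} to say that unblinded bedside nurses record the day-1 SF, and that blinding applies only to the biostatisticians and to any later handling of the data with the arm masked.
2. Give one true statement on whether families know the allocation.
3. In {18a}, accept retrospective entries for the primary outcome only from a dated source record, entered by study number without the arm by the data manager already named in {5d}. Otherwise treat the value as missing under the multiple imputation in {20c}.
4. Report the SF index as an unblinded measurement.

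Do not redefine the day-1 SF as an average over a device-recorded window. Recruitment began on Oct 20, 2023, so a new definition would mix two measures across infants, and the article does not show that the devices store the data. Where device records exist, they can be used to check the charted values. Masked entry cannot undo any effect of knowing the arm on how FiO2 was set or read, which is why item 4 is needed.

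Cost: a formal amendment under {25}, possibly a few more missing values, and loss of the claim of blinded outcome assessment during data collection. Sample size, margin and primary test do not change.

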### Procedure for unblinding if needed {17b}

Blinding was implemented for both outcome assessors and biostatisticians in this trial. Outcome assessors remained blinded throughout the processes of data collection and outcome evaluation to ensure unbiased assessment. Biostatisticians were also blinded during data analysis to minimize analytical bias. In contrast, all clinical personnel and participants were aware of the treatment allocations to preserve the authenticity and integrity of the pragmatic intervention conditions.

## Data collection and management

### Data collection methods {18a} {18b} {19}

In this trial, we have implemented a structured approach to ensure the accuracy and reliability of data collection. A standardized bedside recording form will be utilized throughout the study period. During PS administration, 2–3 designated healthcare staff members will be responsible for conducting the procedure to maintain consistency, while an additional healthcare staff member will oversee the process and meticulously record the data. This dual-layered approach not only enhances the precision of data collection but also minimizes potential errors.

After the use of PS, the monitoring of primary and secondary outcomes will continue, with bedside nurses recording data at several predetermined time points: 1 minutes, 3 hours, 6 hours, 12 hours, and 1 day after PS administration. This ongoing monitoring ensures that any post-trial developments are captured systematically. Furthermore, to ensure the integrity and comprehensiveness of the dataset, the trial leader will retrospectively review and complete any additional data entries. This meticulous methodology underscores our commitment to rigorous data management and the reliability of the trial outcomes. By employing a combination of real-time monitoring and retrospective data completion, we aim to provide a robust and comprehensive dataset that accurately reflects the trial’s findings. This approach not only enhances the validity of our results but also ensures that all relevant data points are captured and analyzed thoroughly.

The trial data will undergo rigorous verification and management under the supervision of the principal investigator (PI). To ensure data integrity and security, all collected data will be stored in a designated area within the department, specifically allocated for this trial. Upon the completion of data collection, the PI will be responsible for summarizing and organizing the data into a structured format, facilitating subsequent analysis and reporting. In addition to data management, the PI will play a pivotal role in maintaining the study’s adherence to protocols. This includes conducting regular training sessions for all trial participants, focusing on procedural accuracy and standardized data collection methods. These training initiatives aim to minimize errors, enhance consistency, and ensure that all participants are well-equipped to follow the study’s guidelines meticulously.

By combining meticulous data management with ongoing participant training, this approach underscores the commitment to maintaining the highest standards of research quality and protocol compliance throughout the trial. This structured methodology not only safeguards the reliability of the data but also reinforces the overall credibility and validity of the study’s findings.

### Confidentiality {27}

The Data Safety and Monitoring Committee, consisting of two principal investigators, is responsible for storing and verifying the authenticity and integrity of the data to ensure the accuracy of the study results.

All participants will be identified by a reference number, which will be used throughout the study. Data will be securely protected during transmission and archiving to ensure patient privacy and prevent data leakage or loss. Any information containing names or other personal identifiers (e.g. consent forms and demographic tables) will be stored separately from the study records identified by the reference number. Contact information will be retained after obtaining consent from the family, for potential follow-up studies (if applicable).

### Biological sample item {33}

Not applicable to this test.

## Statistical methods

### Statistical analysis {20a}

All analyses will be performed using SPSS software (IBM Corp., Armonk, NY, USA). Continuous variables will be summarized as means ± SD or medians (IQR), and categorical variables as *n* (%). The primary outcome, the SF index at 1 day after PS administration, will be evaluated for clinical equivalence between the LMA and INSURE groups using the TOST procedure based on an independent-samples t-test. Equivalence will be concluded if the entire 90% CI of the mean difference lies within the predefined margin of − 0.45 to + 0.45; if normality is not met, a nonparametric test will be applied. Secondary outcomes will be analyzed using t-tests or Mann–Whitney U tests for continuous variables and logistic regression or Fisher’s exact test for binary variables, as appropriate. If baseline imbalances are identified, multivariable linear or logistic regression will be performed to obtain adjusted estimates. A two-sided *P*-value < 0.05 will be considered statistically significant.

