### Sample size {14}

The sample size for this equivalence trial was determined a priori based on the primary outcome—the SF index at 1 day after PS administration. The calculation was performed using EmpowerStats (www.empowerstats.com) and R software (version 4.1.0, R Foundation for Statistical Computing, Vienna, Austria). Based on pre-experimental data, the mean SF index was 4.5 in both the LMA and INSURE groups, with standard deviations of 0.5 and 0.3, respectively, yielding a pooled SD of approximately 0.41. For this equivalence design, the sample size was determined according to a predefined equivalence margin (Δ) of 0.45, which was considered clinically acceptable by expert consensus as it represents less than a 10% difference from the baseline mean value.

Using these parameters (*Δ* = 0.45, SD = 0.41, *α* = 0.05, power = 90%), a two one-sided test (TOST) procedure indicated that a minimum of 23 participants per group was required. Allowing for an anticipated 20% dropout rate, we planned to enroll 29 participants per group, for a total of 58 infants. To facilitate recruitment, the final target sample size was rounded to 60 infants (30 per group).

This methodological approach underscores our commitment to rigorous scientific standards and enhances the reliability and validity of our trial outcomes.

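### If normality fails, the primary equivalence analysis moves to an unnamed nonparametric test with no stated margin, and the planning figures make that branch the likely one

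*Protocol article*

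**What the plan says.** The primary outcome is "The SF index (SpO_2_/FiO_2_) at 1 day after PS administration" (Protocol article, Primary outcome measures). Statistical analysis {20a} sets a TOST built on the independent-samples t-test and gives the decision rule: "Equivalence will be concluded if the entire 90% CI of the mean difference lies within the predefined margin", which runs from -0.45 to +0.45. The same sentence continues: "if normality is not met, a nonparametric test will be applied". Nothing further is said about that case: no named test, effect measure, interval or margin, and no criterion for judging normality.

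The next sentence names Mann-Whitney U, but for secondary outcomes. The section closes with a general two-sided 0.05 significance rule.

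Sample size {14} reports from pilot data that "the mean SF index was 4.5 in both the LMA and INSURE groups, with standard deviations of 0.5 and 0.3, respectively", and uses a "predefined equivalence margin (Δ) of 0.45" expressed as a fraction of the mean.

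**The concern.** The trial is designed to show equivalence. That needs a margin and an interval, or a pair of one-sided tests, on the scale where the margin was set. The article supplies these for the mean difference only. Once the switch is made, the text no longer says what result would count as equivalence.

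If the unnamed test turned out to be an ordinary rank test of difference, the primary question could not be answered. A non-significant result does not show equivalence, and a significant one can arise from a difference in shape when the means are equal.

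This would matter little if non-normality were remote. SF is a ratio with a physical ceiling, however, and the planned mean lies close to it. The branch without a rule is therefore the one the trial should expect to use.

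**Working it through.** **Inputs.** From Sample size {14}: mean 4.5 in both arms, SD 0.5 (LMA) and 0.3 (INSURE), margin 0.45, α 0.05, power 90%, 23 per group before dropout and 30 after rounding. From Statistical analysis {20a}: 90% CI of the mean difference within ±0.45. Assumed, because the article does not state them: FiO2 at least 0.21, SpO2 at most 100%, and normality judged by Shapiro-Wilk at 5%.

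**The plan's own figures.**
- Pooled SD = √((0.5² + 0.3²)/2) = √0.17 = 0.41, as stated.
- A t-based TOST with true difference 0 and 0.025 per side needs 23 per group (power 90.7%), as stated. At 0.05 per side, which the 90% CI implies, 19 suffice and 23 give 95.7%. The stated size is therefore conservative, and sample size is not the problem here.
- 23/0.8 = 28.75, so 29 per group, as stated.

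**Step 1: the ceiling.** Maximum SF = 1.00/0.21 = 4.762. The gap to the planned mean is g = 4.762 - 4.5 = 0.262.
- LMA: 0.262/0.5 = 0.52 SD. A normal distribution would put 1 - Φ(0.524) = 30% of infants above the possible maximum.
- INSURE: 0.262/0.3 = 0.87 SD, giving 1 - Φ(0.873) = 19%.

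**Step 2: the skewness this forces.** For a variable bounded above, with SD s and distance g from mean to bound, skewness is at most g/s - s/g.
- LMA: 0.524 - 1.909 = -1.39, which is marked left skew.
- INSURE: 0.873 - 1.145 = -0.27, which is only mild.
- If 4.5 was rounded from 4.45, the bounds become -0.98 and +0.08. The LMA arm must still be skewed; the INSURE arm need not be.

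**Step 3: how often the switch is triggered.** In data simulated under the ceiling at the planned means and SDs (capped gamma and capped beta shapes), Shapiro-Wilk rejected in 100% of LMA groups. In INSURE groups it rejected in 96-99% at n = 23 and over 99% at n = 30. Mixtures of room-air and oxygen-dependent infants, with means and SDs near but not equal to the planned ones, gave 93-99.9%. Under the planning values at least one arm fails in essentially every trial.

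**Step 4: what a rank test without a margin would do there.**
- *Equal means, planned SDs.* Mann-Whitney gave P < 0.05 in 54% (n = 23) and 63% (n = 30) of trials with capped beta data (lower bound 2.25 assumed), and down to about 36% across the shapes tried. It is responding to shape, not to a mean deficit.
- *Assumed non-responder scenario.* With 33% of LMA and 5% of INSURE infants not responding, the mean deficit is 0.49, outside the margin. Mann-Whitney was non-significant in about 54-63% of trials at 24 to 30 per arm.

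**Step 5: keeping the margin on the mean difference.** With the capped beta data, a Welch 90% CI within ±0.45 had power 93.6% (n = 23) and 97.4% (n = 30) at equal means. At a true difference of -0.45 it declared equivalence in 5.5% and 5.9%. With capped gamma data the figure at the margin was about 10%, and across shapes and sample sizes the range is about 6-11%. A Hodges-Lehmann 90% CI on the beta data declared equivalence in 12% and 14% at a true mean difference of -0.45, because it estimates a different quantity.

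**The case against.** The strongest objection is that the article does not prescribe Mann-Whitney for the primary outcome. A reader might infer it, since it is the only nonparametric test for continuous data named in the section, but it is attached to secondary outcomes. The fallback clause sits in the sentence that sets the margin, so a nonparametric equivalence procedure against ±0.45 may have been intended, and an analysis plan not shown here could name it. This stands as a limit: the supportable statement is that the fallback's test, effect measure and margin are unstated. It does not remove the point, because the article itself commits the primary analysis to the switch and ties its only margin to the mean difference.

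Second, a reader might take the 54-63% miss rate as the trial's expected error. The documents do not support that. The scenario has LMA mean 3.92 and SD 0.85, and INSURE mean 4.41 and SD 0.40, which are not the planning values. The result also depends on shape: with ceiling-skewed data (SD 0.3) and a uniform shift of 0.49, Mann-Whitney misses the deficit in under 0.1% of trials. At the plan's own means and SDs the error runs the other way.

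Third, it is tempting to say that both arms must be strongly skewed. Only the SD 0.5 arm must be.

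Fourth, skewness also affects Welch TOST. This stands: the replacement does not hold exactly 5% at the margin.

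**Conclusion.** The point holds in this form: the primary analysis is committed to a branch with no stated equivalence rule, and the planning figures make that branch close to certain. The near-certainty rests on the physical limits for FiO2 and SpO2, on the pilot mean and SDs being about right, and on a formal normality test such as Shapiro-Wilk at 5%. A laxer or visual criterion could trigger the switch less often.

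The two simulated error rates show that a rank test without a margin can mislead in either direction. They do not predict this trial's error rate, and they do not show that the authors intended such a test.

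**What to change.** In Statistical analysis {20a}, delete the normality switch. State that equivalence is judged in all cases by TOST on the difference in mean SF index, using an unequal-variance (Welch) 90% CI against -0.45 to +0.45. Welch also suits the unequal SDs in Sample size {14}. Add a bootstrap CI for the mean difference as a sensitivity analysis, and report rank tests as descriptive only.

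State the downside: with the skewness implied by the planning values, false equivalence at the margin is about 6-11%, depending on shape and sample size, against a nominal 5%.

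Do not substitute a Hodges-Lehmann interval without justification. It targets a location shift, whereas the margin was set on the mean difference.

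The change is wording only, with no extra data or infants. Protocol amendments {25} provides the route, and it should be made before the outcome data are analysed.

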### Trial design {8}

This trial is a single-center randomized controlled trial. The included samples will be randomized into the experimental group (LMA group) and the control group (INSURE group) by methods of envelopes. The study is an equivalence trial designed to demonstrate that LMA and INSURE are equally effective in the treatment of NRDS using PS.

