### Secondary outcome measures

The SF index before and after the administration of PS.The main monitoring time points are: before PS use and at 1 minute, 3 hours, 6 hours, and 12 hours after PS administration.Time taken for placement.Number of SpO_2_ fluctuations, episodes of bradycardia, and tachycardia during intubation.Whether PS could be aspirated from the stomach after administration.Administration of a second dose of PS due to NRDS (administered in the same manner as the first dose) (ethically assessed).Incidence of pneumothorax.

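### The secondary SF values are compared by unadjusted difference tests, which cannot show similarity; report baseline-adjusted arm differences with confidence intervals instead

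*Protocol article*

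**What the plan says.** All places are in the protocol article.

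- **Trial design {8}:** "The study is an equivalence trial designed to demonstrate that LMA and INSURE are equally effective".
- **Statistical analysis {20a}, primary outcome:** for the SF index at 1 day, "Equivalence will be concluded if the entire 90% CI of the mean difference lies within the predefined margin" of ±0.45.
- **Secondary outcome measures:** SF is also recorded "before PS use and at 1 minute, 3 hours, 6 hours, and 12 hours after PS administration".
- **Statistical analysis {20a}, secondary outcomes:** "Secondary outcomes will be analyzed using t-tests or Mann"–Whitney U tests when continuous. A two-sided P below 0.05 "will be considered statistically significant". No margin or interval rule is given for these outcomes. Multivariable regression is used only if baseline imbalances are found.
- **Sample size {14}:** a "predefined equivalence margin (Δ) of 0.45". The spread is taken from pilot data, "with standard deviations of 0.5 and 0.3, respectively, yielding a pooled SD of approximately 0.41". The planning value is the same for either method: "the mean SF index was 4.5 in both the LMA and INSURE groups". These figures are for 1 day. No SD is given for any earlier time.

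**The concern.** The aim is to show that two delivery methods perform alike, yet the test named for every SF value except the 1-day one asks whether they differ. Failure to find a difference may mean that the arms are similar or that the data are too imprecise, and a P value alone does not say which.

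The early values deserve better because the 1-day value has little room to differ. The planning mean is close to the highest SF possible on room air, whereas entry SF is far below it. Two methods that deliver different amounts of surfactant could have converged by 1 day. The Discussion gives serial SF the role of tracking effectiveness in real time and raises possible drug wastage with the laryngeal mask, so readers will look at these hours.

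Two smaller points follow from the same wording. Pre-surfactant SF is listed among the secondary outcomes, so the general sentence, taken literally, tests it, although any difference before treatment in a randomised trial is chance. And this prognostic measurement enters a model only after an imbalance has been seen, which makes the choice of analysis depend on the data.

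**Working it through.** **Inputs.** Margin 0.45; SDs 0.5 (LMA) and 0.3 (INSURE); mean 4.5; 23 per group required and 30 planned (Sample size {14}). Entry FiO2 at least 0.30 for SpO2 90–94% (Inclusion criteria). Two-sided 0.05 and the 90% CI (Statistical analysis {20a}). SDs of 0.6, 0.8 and 1.0 for the early times are assumptions.

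**1. The plan's own figures.** Pooled SD = √((0.5² + 0.3²)/2) = 0.412, as stated. Exact two one-sided tests with true difference 0, margin 0.45 and SD 0.41 reach 90% power at 23 per group with one-sided 0.025 per test (power 0.907). This reproduces the stated 23. With one-sided 0.05, which matches the 90% CI, 19 suffice, so 23 is conservative. Dropout: 23/0.8 = 28.75, hence 29, also as stated.

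**2. Room to differ.**
- Entry: SF is at most 0.94/0.30 = 3.13.
- Room air: SF is at most 1.00/0.21 = 4.76.
- The planning mean of 4.5 corresponds on room air to SpO2 = 4.5 × 0.21 = 94.5%.

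The 1-day mean is thus 4.76 − 4.5 = 0.26 below the ceiling, which is less than the margin.

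**3. When does non-significance imply a 90% CI inside ±0.45?** With n per arm and 2n − 2 degrees of freedom, the largest non-significant difference is t(0.975) × SD × √(2/n). Its outer 90% limit adds t(0.95) × SD × √(2/n). Setting the sum to 0.45 gives

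SD = 0.45 / [(t(0.975) + t(0.95)) × √(2/n)].

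- n = 30: 0.45 / [(2.002 + 1.672) × 0.2582] = 0.47
- n = 23: 0.45 / [(2.015 + 1.680) × 0.2949] = 0.41

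At 30 per arm:

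| SD | Largest non-significant difference | Its outer 90% limit |
|---|---|---|
| 0.41 | 0.21 | 0.39 (inside) |
| 0.5 | 0.26 | 0.47 (outside) |
| 0.8 | 0.41 | 0.76 (outside) |
| 1.0 | 0.52 | 0.95 (outside) |

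The SD of 0.5 is the LMA arm's own 1-day value.

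**4. How often is a true difference of 0.45 missed?** This uses the two-sided 0.05 t-test, noncentral t with noncentrality 0.45/(SD × √(2/n)).

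| SD | 30 per arm | 23 per arm |
|---|---|---|
| 0.41 (documented, pooled, 1 day) | 1.3% | 4.7% |
| 0.5 | 7.1% | 15.3% |
| 0.6 (assumed) | 18.5% | 29.9% |
| 0.8 (assumed) | 42.8% | 53.7% |
| 1.0 (assumed) | 59.7% | 68.0% |

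**5. What adjustment buys.** Adjusting for a baseline with correlation r multiplies the variance by about 1 − r². At r = 0.5 (an assumption) this is 1 − 0.25 = 0.75, a 25% saving.

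**6. Does ±0.45 carry over to early times?** Sample size {14} justifies 0.45 against the mean of 4.5, of which it is 0.45/4.5 = 10%. Against the entry maximum it is 0.45/3.13 = 14%. The justification does not transfer as it stands.

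**The case against.** The strongest reply is that the harm is hypothetical. A reader might infer that a non-significant result at 3 to 12 hours will be taken as proof of equivalence, or that such results are bound to be uninformative. The document supports neither. It ties the equivalence conclusion to the 90% CI at 1 day and nowhere says how a non-significant secondary result will be read. At the only documented pooled SD, 0.41, a non-significant t-test with 23 to 30 per arm does put the 90% CI inside the margin. The larger miss rates need early SDs that the protocol does not give. This stands, and it limits the point to a conditional one.

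Other replies also stand:

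- Separate two-sample tests at each time use one value per infant, so within-infant correlation does not invalidate them. A repeated-measures model is one option, not a requirement.
- Baseline information is not simply discarded, because conditional adjustment is provided. The criticism is of the trigger.
- Separate tests, and a test of pre-surfactant SF, are inferred from a general sentence that applies its methods as appropriate.
- No early SF data are given, so the ceiling shows only that earlier times have more room to differ, not that they hold most of the information.
- Applying ±0.45 at early times would often be inconclusive. With 30 per arm and no true difference, the chance that the 90% CI falls inside it is 0.78, 0.39 and 0.09 at SD 0.6, 0.8 and 1.0.

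A statistical analysis plan may add detail on modelling. What remains is a method that the article itself fixes: difference tests for these values, with adjustment left to an observed imbalance.

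**Conclusion.** The point holds as a minor improvement to secondary analyses. The named tests do not show similarity, and in a trial with this aim the early SF comparisons would be more useful as estimates with intervals.

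The size depends on an SD that the protocol does not give. Up to about 0.47 with 30 per arm, or 0.41 with 23, a non-significant t-test and a 90% CI inside ±0.45 go together. Above that they do not, and for assumed SDs of 0.6 to 1.0 a true difference of 0.45 goes undetected in about 18.5% to 60% of trials with 30 per arm. These figures assume normal data, equal SDs and equal arms. The 1-day equivalence test and the conclusion drawn from it are unaffected.

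**What to change.** In Statistical analysis {20a}:

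1. For SF at 1 minute, 3, 6 and 12 hours, report the arm difference with a CI from a model with prespecified adjustment for pre-surfactant SF. This can be ANCOVA at each time, or one repeated-measures model with arm-by-time terms. It replaces the adjustment triggered by an observed imbalance.
2. State that P ≥ 0.05 on a secondary outcome is not evidence of equivalence.
3. Show ±0.45 at the early times only as a reference, unless a margin is justified for them.
4. Summarise pre-surfactant SF descriptively, without a test.
5. Keep the 1-day two one-sided tests as the primary analysis.

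The cost is a few lines of wording and slightly more analysis work. If the repeated-measures model is chosen, a covariance structure must be specified for about 60 infants; ANCOVA at each time avoids that. No new data are needed. Recruitment is expected to finish in June 2026 and no interim analysis is planned, so the change can be fixed by amendment before the outcomes are analysed.
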